### Sample size

We assume that a total antibiotic prescription rate of 12% (rate of high prescribers in the predecessor project RESIST, unpublished data) will be observed in the control group. This rate is expected to be reduced to 8.7% in group A, to 8% in group B, and to 7% in group C. Since all interventions shall be compared to the control, we adjust for multiple testing via the Bonferroni correction and hence the type 1 error is set to 1.67% (two-sided). A Poisson model was used for sample size calculation. To be able to show the effect assumed for the comparison between the control group and group A with a power of 80%, 2000 practices are required in both groups. Due to the feasibility, maximal 1250 practices can be included in group C for comparison to the control. Thereby a power of 98.8% can be gained. Group B consists of 2000 practices to include all remaining eligible practices in all nine participating regional ASHIP. For the comparison between the control group and group B, a power of 94.6% can be gained. This sample size calculation refers to the intention-to-treat (ITT) population. This population includes all randomized practices regardless of whether they accept the offer of training in groups B and C. However, we are also interested in the per-protocol (PP) population which is analyzed within a secondary analysis. The PP population includes only those practices in groups B and C that participated in the training courses according to protocol. Thus, only the assumed effects between the control group and groups B and C change. We assume that in group B, the rate in this population can be reduced to 7.5%. Furthermore, we assume a participation rate between 30% and 40%, i.e., between 580 and 800 practices participate in the online training. Assuming this difference and the Bonferroni adjusted type 1 error of 1.67 a power between 80% and 89% can be gained. In group C, we assume a participation rate between 17% and 20%, i.e., between 215 and 250 physicians will presumably participate in the peer-moderated online training. Under the assumption of a reduction to 6% and the Bonferroni adjusted type 1 error of 1.67 a power between 80% and 85.8% can be gained See Fig. 2.

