### Statistical methods

All prescription rates for the primary and secondary outcomes are presented descriptively for the entire sample and separately according to groups. Sampling units are practices. A negative binomial regression model will be used to evaluate whether the change of prescription rates differs between control and intervention(s) (primary outcome). The negative binomial model is used because we assume that the mean and variance for prescription rates will be different (also seen in the RESIST study). Hereby, the number of antibiotic prescriptions after the intervention(s) is considered as the dependent variable, the number of patients is treated as the offset variable, the grouping variable and the area of the respective regional ASHIP are fixed effects, and the rate before the introduction of the intervention(s) is a covariate in the model. Although we used the Bonferroni-corrected significance level within the sample size calculation, we will evaluate the primary outcome with the less conservative Dunnett test which uses the information that the three interventions will be compared to the same control. The resulting adjusted *p* values will be compared to the global significance level of 5%.

The secondary outcomes will be exploratively analyzed using a negative binomial model without adjustment for multiple testing. Thereby, the dependent variables are the prescription rates for cephalosporins and fluoroquinolones, respectively. The fixed effects are the grouping variable, the area of the respective regional ASHIP, and the rate before the introduction of the intervention(s) for cephalosporins and fluoroquinolones, respectively. The number of patients serves as the offset variable.

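### Step-down Dunnett would replace the planned Dunnett test at the same 5% family-wise error with equal or higher power; the gain for arm A runs from nil to about 8 points, depending on the true effects

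*Protocol article*

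**What the plan says.** Under Sample size, the control rate is set first ("We assume that a total antibiotic prescription rate of 12" percent), then the rates in the arms: "This rate is expected to be reduced to 8.7% in group A, to 8% in group B, and to 7% in group C". The calculation is Bonferroni-adjusted ("the type 1 error is set to 1.67% (two-sided") and Poisson-based ("A Poisson model was used for sample size calculation"). Arm A fixes the size: "with a power of 80%, 2000 practices are required in both groups". For B the article states "For the comparison between the control group and group B, a power of 94.6% can be gained", and for C, with 1250 practices, 98.8%.

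Under Statistical methods, Bonferroni is dropped for the analysis: "we will evaluate the primary outcome with the less conservative Dunnett test". The reason given is that the three interventions share one control. The adjusted p "values will be compared to the global significance level of 5" percent. Neither a single-step nor a step-down form is named. The same section makes only the intention-to-treat primary analysis confirmatory and asks for rate ratios with 95% confidence intervals, without calling them simultaneous.

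**The concern.** The sponsor chose Dunnett over Bonferroni to avoid needless conservatism. Single-step Dunnett recovers only part of what is available, because every arm faces the three-comparison critical value even after the other arms have been shown to work. Step-down Dunnett lowers the hurdle after each rejection.

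Arm A, the feedback letter alone, has the smallest assumed effect and the lowest planned power. B and C are expected to be rejected first, and that is the situation in which step-down testing helps the remaining arm most. At stake is a confirmatory result for A that the 5% error budget would have allowed. No other analysis is confirmatory, so a missed result could not be recovered elsewhere.

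**Working it through.** **Inputs (Sample size section).** Rates: control 0.12, A 0.087, B 0.08, C 0.07. Practices: 2000, 2000, 2000, 1250. Bonferroni level 0.05/3 two-sided, so z = 2.394.

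**1. Reproduce the stated power.** The form that fits is a difference of two Poisson rates with one unit of exposure per practice: δ = (r0 − r1)/√(r0/n0 + r1/n1), power = Φ(δ − 2.394).

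- A: 0.033/√(0.000060 + 0.0000435) = 3.244; power 80.2% (stated 80%)
- B: 0.040/√(0.000060 + 0.000040) = 4.000; power 94.6% (stated 94.6%)
- C: 0.050/√(0.000060 + 0.000056) = 4.642; power 98.8% (stated 98.8%)

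**2. Dunnett critical values.** Under the null the correlation of two comparisons is √[n1/(n1+n0)] × √[n2/(n2+n0)]. This is 0.50 for A with B and 0.44 for either with C. The two-sided 5% values are 2.356 for three arms, 2.21 to 2.22 for two, and 1.96 for one.

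**3. Single-step power.** Φ(δ − 2.356) gives A 81.3%, B 95.0%, C 98.9%. Moving from Bonferroni to single-step Dunnett therefore gains A about 1 point (80.2% to 81.3%).

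**4. Step-down power.** The procedure was run as a closed max-|Z| test, with two million simulated draws per scenario. Power for A:

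| Scenario | Single-step | Step-down | Gain (points) |
|---|---|---|---|
| Planned rates | 81.3% | 89.5% | about 8 |
| All standardised effects halved | 23% | 30% | about 7 |
| All rate reductions halved | 21.3% | 27.4% | about 6 |
| All arms at A's rate | 81.3% | 86.1% | about 5 |
| Only A works | 81.3% | 81.4% | about 0.1 |

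Under the planned rates B goes from 95.0% to 97.0%, C from 98.9% to 99.2%, and all three significant from 79.3% to 88.8%. The ceiling for A, at an unadjusted 5%, is Φ(3.244 − 1.96) = 90.0%.

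**5. Error control.** Under the global null the family-wise error is 4.99% for both forms. With A null and B and C effective, A is falsely rejected in 1.9% of draws with single-step and 4.7% with step-down. No draw lost a single-step rejection. That must hold, because no step-down critical value exceeds the single-step one.

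**6. How far this carries to the actual analysis.** The planned model is negative binomial with the number of patients as offset. Patients per practice (m) and dispersion (k) are not given, so these are assumptions. On the log scale, z for A = ln(0.12/0.087)/√[(1/(0.12m) + k)/2000 + (1/(0.087m) + k)/2000].

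- m = 5, k = 1: z = 5.89; power 99.98% at 2.356 and above 99.99% at 1.96
- m = 50, k = 1: z = 9.29; power near 100% at either value

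At the planned effect the gain is then below 0.1 point.

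**The case against.** The case for leaving the text alone is substantial.

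- **The plan is valid.** It prespecifies a standard many-to-one test with strong error control, and A's 80% target is met (80.2% Bonferroni, 81.3% single-step). A reader might infer an error or an underpowered comparison. The documents support neither. This point stands in full.
- **The form of the test is inferred.** Comparing adjusted p values with 5% fits a step-down version equally well, and an unseen SAP could specify one. Single-step is still the ordinary meaning of an unqualified Dunnett test, so naming the form is useful either way.
- **A flat 8-point loss is overstated.** A reader might take 8 points as what the trial gives up for A. That figure needs the planned effects in B and C as well as unit exposure per practice, and the analysis model does not use unit exposure. The gain also shrinks if B and C do little more than the letter. Take the article's own participation rates and per-protocol rates, and assume non-participants sit at A's 8.7%. B is then 0.30 × 7.5 + 0.70 × 8.7 = 8.3% to 0.40 × 7.5 + 0.60 × 8.7 = 8.2%. C is 0.17 × 6 + 0.83 × 8.7 = 8.2% to 0.20 × 6 + 0.80 × 8.7 = 8.2%. A's gain becomes 6.7 to 7.0 points.
- **There is a trade-off.** Single-step Dunnett has directly matching simultaneous intervals; step-down has no simple ones. Preferring matching intervals is defensible, but the article does not ask for simultaneous intervals.

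**Conclusion.** The point holds as an inexpensive improvement to a valid plan. Step-down Dunnett is at least as powerful in every configuration at the same 5% family-wise error. The size for arm A depends on the other arms and on the scale of the true effects: from about 0.1 point if only A works, through 5 to 7 points in the intermediate cases, to about 8 points under the planned rates, all on the Sample size section's unit-exposure Poisson basis. With several patients per practice (an assumption) and the planned effect, the choice makes practically no difference. The practical value is protection if effects are smaller than planned and more than one arm works. The absolute powers would differ under the negative binomial model with a baseline covariate; the ordering of the two procedures would not.

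**What to change.** In Statistical methods, and in the SAP, name the step-down Dunnett procedure. Order the three arm-versus-control statistics from the negative binomial model by absolute size. Test the largest against the three-arm Dunnett value, the next against the two-arm value and the last against 1.96, stopping at the first non-rejection. Compare the step-down adjusted p values with 5%. Add that the reported 95% confidence intervals are not simultaneous and may not match the step-down decisions; an interval may include a rate ratio of 1 beside a significant adjusted p value.

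The cost is a sentence or two, fixed before unblinding, with no new data and no more practices. The one thing given up is the simple matching simultaneous intervals of the single-step test.

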### Risk of bias

There are several risk factors that could influence the success of the project: It is possible that there is too little acceptance on the part of the GPs contacted, resulting in low-participation rates in the interventions offered. In the case of peer-moderated training, this could lead to heterogeneous group sizes and the desired intercollegiate exchange not being able to take place due to a low number of participants. To counteract this, a sufficiently high number of GPs is contacted, and the content of the letters is closely coordinated with the regional ASHIP experienced in this field. Participation is also incentivized by an expense allowance. In addition, the training courses are conducted online in a format similar to quality circles to maximize acceptance among GPs. Another external risk factor that cannot be influenced is a higher or lower level of disease activity in the period under review (wave of flu, Sars-CoV-2 pandemic, other disruptive effects, or overlapping events) than in the preintervention period used for the evaluation. As a countermeasure, in addition to a pre-post comparison with an extended comparison period, a comparison to non-contacted high prescribers in the participating regions (Group D as a “real control group”) is also carried out here.

### Process evaluation

The process evaluation of the interventions tested in ElektRA is carried out using a mixed-methods approach, i.e., combining qualitative and quantitative research methods. The focus is on the question of how the intervention contents are perceived, accepted, and implemented in everyday practice by the GPs. In addition, the non-participants, i.e., non-responders to the project or refusers of the interventions, will be examined more closely. The question, which barriers prevail both in terms of participation and reducing the prescription of antibiotics where it is appropriate and safe will be investigated.

The selection of the participating GPs for the qualitative survey follows the principles of purposeful sampling, i.e., the composition of the sample corresponds to certain socio-demographic criteria (e.g., age, gender, practice size, degree of urbanization). At the heart of qualitative research is a systematic, open approach both in terms of study design and data analysis. To analyze GP readiness for implementation, 1–3 (telephone) interviews per participating ASHIP and per intervention group will be conducted with the participating physicians. With 9 participating regional ASHIP, about 70 interviews will take place. According to our experience, these will have a duration of approx. 20–30 min. The interviews will be conducted by an experienced interviewer. All interviews will be audio-recorded, pseudonymized, and fully transcribed. The data collection will be finished as soon as the generated hypotheses are saturated [31]. The analysis takes place at the content level. In the end, a system of categories is created that allows for summarizing the most important results of the interviews. The analysis is software-supported (e.g., with NVivo 10).

The results of the qualitative study will be transferred into a questionnaire in the following, which will be adapted for the three intervention groups. In this way, the hypotheses developed in the qualitative process evaluation will be investigated on a representative sample of the participating GPs. Further, to reach the non-responders, a questionnaire (as low-threshold as possible) will be sent to all high prescribers (within groups B and C) who have decided not to participate in the respective training offered. In this questionnaire, participation in an in-depth interview is advertised.

### Study registration

The study has been registered with Current Controlled Trials Ltd. with the reference ISRCTN95468513.

### Trial status

In August 2022, final work on the implementation of the online training will be completed and all project documents will be prepared. Recruitment of participants will start in September 2022.

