### Participants

The Zi uses a summative score to determine potentially eligible GPs and GP practices based on German prescription and outpatient claims data before intervention (T0, October 2020–September 2022). The maximum score value is six. A GP or GP practice obtains one additional point if its own value in one of the aspects exceeds the 75% percentile of antibiotic prescribing within the respective region. Here, a region represents the area for which a participating ASHIP is responsible. In Germany, there are in total of 17 of those regions, 9 of which are participating in this study. For inclusion, more than two points are necessary. The aspects listed in Table 1 are used for score formation.

**Table 1 Tab1:** Aspects considered for score formation

1	Overall prescription rate (ratio of patients with antibiotic prescriptions to patients with any prescription)
2	Prescription rate for upper respiratory tract infections (ratio of patients with upper respiratory tract infection to antibiotic prescriptions for these patients)
3	Prescription rate for lower respiratory tract infections (ratio of patients with lower respiratory tract infection to antibiotic prescriptions for these patients)
4	Prescription rate of fluoroquinolones (2 points possible): total prescription rate of fluoroquinolones (ratio of patients with fluoroquinolone to patients with antibiotic) and/or fluoroquinolone prescription rate for urinary tract infection (ratio of urinary tract infection patients with fluoroquinolone to urinary tract infection patients with antibiotics)
5	Prescription rate of cephalosporins (ratio of patients with cephalosporin to patients with antibiotics)

After identification, the GPs or GP practices meeting the inclusion criteria are randomized and stratified by region. As identification is based on pseudonymized data, an independent trust center will generate study pseudonyms that will enable all participating regional ASHIP and the Zi to communicate about identified entities and allow the ASHIP to re-identify these eligible GPs or GP practices and contact them. The Zi on the other hand will always exclusively work with pseudonymized data to compile all further analyses, e.g., those necessary for providing GP-specific prescription feedback. Physicians who have already participated in the RESIST Innovation Fund project [13] are excluded because they have already received e-learning on optimizing antibiotic prescribing.

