### Recruitment

Nine regional ASHIPs participate in the trial (Baden-Württemberg, Bavaria, Bremen, Hesse, Lower Saxony, North Rhine, Saarland, Schleswig-Holstein, Westphalia-Lippe). Based on the procedure described above, eligible GPs will be contacted by their respective regional ASHIP with a letter containing social norm feedback and in case of intervention groups B and C an invitation to participate in an online training or an online peer-moderated training.

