### Control group

GPs randomized to the control group will not be contacted or informed about the study. Hence, they will treat their patients as usual.

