### Outcomes

The primary outcome is the overall rate of antibiotic prescriptions, measured as the proportion of patients with antibiotic prescriptions out of all patients with prescriptions within the nine regional ASHIPs before intervention (October 2020–September 2022) and after it officially starts (October 2022–December 2023). All interventions are completed by December 2022. The changes in prescription rates between those two-time frames are compared between the control group and the interventions. Effects measured at this level are very robust, as neither imprecision in diagnosis coding (ICD 10) nor possible changes in coding behavior have an influence on this outcome. The same applies to the secondary outcomes. Secondary outcomes are the overall prescription rates before and after the intervention for cephalosporins and fluoroquinolones, respectively. The choice of these drug groups is based on the European Surveillance of Antimicrobial Consumption (ESAC) quality indicators for the outpatient sector [25] See Fig. 1.

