**Fig. 2 Fig2:**
[figure not shown]
CONSORT flow diagram, estimations on eligibility are based on data of 2020, T0 data from October 2020 to September 2022 is analyzed retrospectively. Source: http://www.consort-statement.org/, Version of 2010 (12.11.2021)

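### Eligibility and baseline use data through September 2022, but recruitment by feedback letter starts in September 2022, so the eligibility window cannot be used as written and the baseline may include post-letter data in arms A–C

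*Protocol article*

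**What the plan says.** All references are to the protocol article.

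- **Eligibility data (Participants).** The score is "based on German prescription and outpatient claims data before intervention (T0, October 2020–September 2022").
- **Order of steps (Participants).** "After identification, the GPs or GP practices meeting the inclusion criteria are randomized and stratified by region". Trial design gives the same sequence (T0 data, identification, randomization, contact) and places the 15-month T1, from October 2022, after randomization.
- **Start of recruitment (Trial status).** "Recruitment of participants will start in September 2022".
- **What recruitment is (Recruitment).** "eligible GPs will be contacted by their respective regional ASHIP with a letter containing social norm feedback". For arm A this letter is the whole intervention. For arms B and C it is the feedback plus an invitation to training.
- **Control group.** "GPs randomized to the control group will not be contacted or informed about the study".
- **Before and after periods (Outcomes).** The before period is October 2020 to September 2022. The after period begins "after it officially starts (October 2022–December 2023").
- **Primary model (Statistical methods).** "the rate before the introduction of the intervention(s) is a covariate in the model".
- **Length of baseline (Data basis).** At least eight quarters of baseline and five of follow-up.
- **Fig. 2 caption.** Eligibility estimates rest on 2020 data, and "T0 data from October 2020 to September 2022 is analyzed retrospectively".

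**The concern.** T0 has two jobs. It decides who counts as a high prescriber, and it supplies the baseline rate that the primary model adjusts for. Both need T0 to be closed before any GP is contacted. The dates given put the first contact inside the last month of T0.

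For eligibility, the stated rule then cannot be carried out. The score compares each practice with the regional 75th percentile on several aspects and requires more than two points, so the data period helps determine who enters the trial. A reader cannot tell which period was used.

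For the baseline, a letter sent in September acts on part of the before period in three arms and not in the fourth. Adjusting for a baseline that treatment has already lowered removes part of the treatment effect.

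**Working it through.** **1. The plan's own count of quarters.** October 2020 to September 2022 is 24 months: 1 quarter of 2020 + 4 of 2021 + 3 of 2022 = 8 quarters. October 2022 to December 2023 is 15 months: 1 + 4 = 5 quarters. Total 8 + 5 = 13, as stated in Data basis. T0 therefore contains exactly the minimum of eight quarters. Dropping July–September 2022 leaves seven unless the baseline starts earlier.

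**2. Can the eligibility score be complete in time?** The required order is: data to 30 September 2022, then score, then randomization, then letter.
- With letters in September (Trial status read with Recruitment), the score would have to be finished before its last month of data exists.
- With all letters in October, the problem remains. Trial design puts T1, which begins in October 2022, after randomization. Randomization would then be due about when the last T0 quarter closes, with no time to extract and score that quarter. The article gives no data lag; any lag makes this worse.

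On either reading, the sample cannot have been selected on the stated window.

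**3. Size of a baseline overlap.** Inputs from Sample size: 12% in control and 8.7%, 8% and 7% in arms A, B and C. The letter-only effect is that of arm A: (12 − 8.7)/12 = 27.5%. Assumptions not in the document: every letter arrives on 1 September, the full letter effect is immediate, and the 24 months carry equal weight.

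- Understatement of the baseline in A–C: 0.275/24 = 1.15%.
- Expected baseline: (23 × 12% + 1 × 8.7%)/24 = 11.86% instead of 12%, a ratio of 0.9885.

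**4. Effect on the rate ratio.** If log baseline enters with coefficient b, the estimated log rate ratio is the true one minus b × ln(0.9885), where ln(0.9885) = −0.0115. With b = 1:

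| Arm | Assumed rate ratio | Estimated | Share of log effect lost |
|---|---|---|---|
| A | 0.725 | 0.725/0.9885 = 0.733 | 0.0115/0.3216 = 3.6% |
| B | 0.667 | 0.667/0.9885 = 0.674 | 0.0115/0.4055 = 2.8% |
| C | 0.583 | 0.583/0.9885 = 0.590 | 0.0115/0.5390 = 2.1% |

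Milder cases for arm A: half of September affected with b = 1 gives 0.729 (1.8% lost). A quarter of September with b = 0.5 gives 0.726 (about 0.4% lost). With no letter before 1 October the loss is zero.

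**5. Power.** A two-rate Poisson calculation without a baseline term reproduces the stated ITT figures: 80.2% for A (stated 80%), 94.6% for B and 98.8% for C. The timing conflict does not touch them.

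**The case against.** The best defence is that the methods text is consistent on intent. Outcomes labels October 2020 to September 2022 as the time before intervention and puts the official start in October 2022. Statistical methods defines the covariate as the rate before the interventions were introduced. Against this stands one forward-looking sentence in Trial status that gives a month and no mailing day. It might cover only preparatory steps or a mailing on the last days of September. The Fig. 2 caption also hints that earlier data were used, and a condensed article may leave extract dates to the full protocol.

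Much of this stands for the baseline: contamination is possible, not shown, and it may be nil. It does not rescue the eligibility window. Even preparatory steps such as re-identification of GPs need the score to be finished. The caption speaks of estimates and does not amend Participants; if it is read as the basis for selection, it contradicts that section. Nor is this an omitted detail: the article states dates that conflict.

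Two stronger readings are tempting and are not supported:
- A reader might infer that eligibility would be recomputed later on data the letters had influenced, so that membership of the analysis set depends on arm. Nothing says so. Randomization follows identification, Sample size defines the ITT population as all randomized practices, and only the ITT result is confirmatory.
- A reader might apply arm C's larger assumed reduction to September. That figure belongs to feedback plus an offer of peer-moderated training. On receipt only the letter can act, and the plan's figure for the letter alone is 27.5%.

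**Conclusion.** The point holds as an internal contradiction with a small possible effect on the results. The firm part is eligibility: the window given in Participants cannot have been available before randomization, and the article names no usable alternative. The conditional part is the baseline: if any letters go out in September, the covariate contains up to one post-letter month in A–C and none in control. The upper bound is a baseline understated by about 1.15%, which moves arm A's rate ratio from 0.725 to at most 0.733. This rests on the assumptions in steps 3 and 4 of the working, each of which pushes the figure up. The direction is toward the null, so the overlap would not create a false positive. If all letters go out from October, the bias is zero and the Trial status sentence is the one that is wrong.

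**What to change.** 1. Reconcile Trial design, Participants, Outcomes, the Fig. 2 caption and Trial status, so that the data cut-off for eligibility, the randomization date and the date of the first letter are stated once and in a possible order.
2. Name as the eligibility window the last complete quarters actually available at randomization.
3. End the baseline covariate, in all four arms, at the last complete quarter before the first letter. July 2020 to June 2022 would be 2 + 4 + 2 = 8 quarters, which meets the minimum in Data basis and contains each calendar quarter twice. With five follow-up quarters the total is still 13, and July–September 2022 falls in neither period.

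The cost is wording, a one-quarter shift in the data extract and a slightly older baseline. The Fig. 2 caption indicates that 2020 data are held, and no new data collection is needed.
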